### Participants

As to eligibility for this protocol, the inclusion criteria are the following: age >18 years; multidomain disability as a consequence of first-ever unilateral ischemic stroke documented by computerized tomography scan or magnetic resonance imaging; and no more than 3 months since stroke onset; ability of patient and/or caregiver to understand the instructions provided for self-rehabilitation. Exclusion criteria are the following: inclusion in other trials; Mini Mental State Examination score <24/30 (10); drug addiction; and other neurological or orthopedic conditions limiting the inclusion in this protocol. Further eligibility criteria for WP2 are cognitive disability with adequate comprehension skills (people with limited attention span excluded). As to other additional eligibility criteria, WP3 will include patients with stroke who are able to walk and have adequate comprehension skills once they have reached the chronic phase of illness. An extra eligibility criterion for WP4 is the presence of painful conditions. The study does not include vulnerable populations such as prisoners, legally interdicted persons, or institutionalized people.

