Oxford Cognitive Screen	✓	✓	✓	✓	✓
Barthel Index	✓	✓	✓	✓	✓
Volumetric analysis of the stroke	✓				
Side and site of stroke	✓				
DTI	✓				
fMRI	✓				✓
MEP and cortical excitability to TMS	✓				✓
SSEP	✓				✓
EEG	✓		✓		
MFI	✓		✓		
DEXA			✓		
Microbiota			✓		
Biochemistry and miRNA analysis	✓				✓
Usual care	✓	✓	✓	✓	✓
Intensive self-rehabilitation program	✓	✓	✓	✓	✓
Physiatric evaluation	✓	✓	✓	✓	✓
Video analysis and energetic cost of the gait	✓	✓	✓	✓	✓
Psychological evaluation scales	✓	✓	✓	✓	✓
Informed consent	✓	✓	✓	✓	✓

*DTI, Diffusion Tensor Imaging; fMRI, functional Magnetic Resonance Image; MEP, Motor evoked potential; SEP, Somatosensory evoked potential; TMS, Transcranial Magnetic Stimulation; EEG, Electroencephalography; MFI, Multidimensional Fatigue Inventory; DEXA, Dual X-ray Absorptiometry; miRNA, microRNA. °Time from the enrollment*.

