### Sample Size

We estimated that 88 subjects, 44 patients per group, would provide 80% power (α level 5%) to detect a difference of 7 points (SD 11.6) on the FMA, the primary outcome, between the groups (26). Considering a dropout rate of 10%, we planned to enroll a total of 97 patients in this study.

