### Data Analysis

Adequate descriptive statistics will be produced, including frequency, mean, median, standard deviation, interquartile range, and confidence intervals, for the demographic data and outcome measures at each time point. As to WP1, the comparison between groups, in terms of self-rehabilitation vs. usual care, with regard to the outcomes considered at each time point of the various evaluation times, will be performed using parametric (e.g., *t*-test, ANOVA) and/or non-parametric statistics, such as the Kruskal-Wallis test or the Mann-Whitney test, depending on the data distribution. Correlation and regression analyses will also be performed between neuroimaging data, neurophysiological variables, and clinical outcomes at different time points. As to the other WPs (2–7), comparisons between groups at different times will be assessed using parametric tests, such as the Student *t*-test and ANOVA, or non-parametric tests, such as the Kruskal-Wallis test and Mann-Whitney test, depending on the data distribution. For each variable considered, both longitudinally and transversely, correlation and regression analyses will also be performed. Moreover, for each WP we will perform longitudinal intragroup comparisons at different times by means of parametric tests, such as the *t*-test and ANOVA and/or non-parametric tests, such as the Friedman test and the Wilcoxon test, depending on data distribution. The statistical analysis will be performed using the Statistical Package for Social Science SPSS® version 26.0 software for Macintosh (SPSS Inc., Chicago, IL, USA). For all statistical tests, the significance level is set at *p* < 0.05.

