## Discussion

This trial will evaluate and follow up stroke patients from subacute stroke to the chronic phase, up to 1 year after stroke onset. It will deal with the effects of an intensive self-management rehabilitation protocol and a related set of biomarkers. In our view it will add some important pieces of evidence to overcome current conceptual limitations on long-term recovery models, upon which the usual care pathway of stroke rehabilitation is based. Another aspect that will be investigated by this study is the role of training intensity on long-term recovery after stroke, a point that will be further strengthened by the moral contract between patients and therapists (12). As suggested in the literature, intensity is a key element of stroke rehabilitation in order to achieve greater training effects (2, 27). In addition, a pattern of biomarkers related to post-stroke recovery and neurorehabilitation outcome will be useful to detect those patients with greater potential for recovery. Despite the fact that some of these biomarkers have been previously reported to offer information on stroke rehabilitation outcome, the prognostic relevance of their combination has never been explored to date and may be important for defining future long-term personalized medical rehabilitation programs. The possible main problems concerning the conduct of the study will be the number of patients enrolling, this being a single center study, the long follow-up duration (1 year), and the multifactorial/multimodal approach to evaluate patients; (that is, many different outcomes will be considered).

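### The between-arm FMA comparison is set as separate per-visit tests, t-test or Mann-Whitney by data distribution, with no adjustment for baseline FMA: valid, but it forgoes precision and leaves the effect measure open

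*Protocol article*

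**What the plan says.** The Data Analysis section of the protocol article sets the WP1 comparison of self-rehabilitation with usual care at each evaluation time. The tests are parametric (t-test and ANOVA as examples) and/or "non-parametric statistics, such as the Kruskal-Wallis test or the Mann-Whitney test, depending on the data distribution". No covariate is named for this comparison. The WP1 correlation and regression analyses relate imaging and neurophysiology to clinical outcomes. The longitudinal comparisons are within groups only.

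The Sample Size section states that 44 patients per group "would provide 80% power (α level 5%) to detect a difference of 7 points (SD 11.6) on the FMA". It does not say whether 11.6 is the SD of a score or of a change.

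Table 1 schedules the FMA at T0 and at T1 to T4. Randomisation is 1:1, balanced and restricted, with no stratification factor stated. Patients enter with "no more than 3 months since stroke onset". The Table 1 footnote defines the visit times as "Time from the enrollment", while the Discussion describes follow-up as "up to 1 year after stroke onset". No visit is named as the primary one.

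**The concern.** The test named for the primary outcome makes no use of the T0 score, although that score is scheduled for every patient. Baseline FMA can be expected to correlate with later FMA. The Participants section sets no FMA limits for entry, and no stratification on severity is stated. So nothing stated in the design or the between-arm comparison deals with baseline severity.

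Three things are at stake:

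- **Precision.** Variation that the baseline score could explain stays in the error term.
- **This trial's estimate.** With about 44 patients per arm, a chance difference in baseline FMA carries over into the follow-up difference.
- **What is estimated.** A t-test addresses a difference in means, the scale of the 7-point target. Mann-Whitney addresses a rank comparison and does not estimate that difference. Choosing by the observed distribution lets the data decide which question is answered, and the and/or wording would allow both.

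**Working it through.** **Inputs.** From Sample Size: difference d = 7, SD = 11.6, alpha = 0.05, 44 per arm. Two-sided testing is assumed because the article does not state sidedness; it reproduces the stated number. The correlation r between baseline and follow-up FMA is not given, so a range is assumed.

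**1. The plan's own figure.** n per arm = 2 × SD² × (1.960 + 0.842)² / d² = 2 × 134.56 × 7.85 / 49 = 43.1, rounded up to 44, or 88 in total. This agrees with the article. The exact two-sample t-test at 44 per arm has 79.9% power (80.8% by the normal approximation). The sample size is therefore that of an unadjusted comparison.

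**2. Reading A: 11.6 is the SD of the follow-up score, and the score is tested.** Adjustment for baseline gives residual SD = 11.6 × √(1 − r²). Power is from the t-test at 44 per arm, ignoring the one degree of freedom spent on the covariate.

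| r | Residual SD | Power |
|---|---|---|
| unadjusted | 11.60 | 79.9% |
| 0.3 | 11.07 | 83.5% |
| 0.5 | 10.05 | 89.8% |
| 0.6 | 9.28 | 93.8% |
| 0.7 | 8.28 | 97.5% |

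**3. Reading B: 11.6 is the SD of change from T0, and change is tested.** With equal SDs at both visits, the raw-score SD is 11.6 / √(2(1 − r)). Multiplying by √(1 − r²) gives an adjusted residual SD of 11.6 × √((1 + r)/2).

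| r | Residual SD | Power |
|---|---|---|
| change score, no adjustment | 11.60 | 79.9% |
| 0.5 | 10.05 | 89.8% |
| 0.6 | 10.38 | 87.9% |
| 0.7 | 10.69 | 85.9% |

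Here the gain shrinks as r rises, because the change score already uses the baseline.

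**4. Reading C: 11.6 is the SD of change, but the raw score is tested.** At r = 0.7 the raw-score SD is 11.6 / √0.6 = 15.0. The unadjusted test then has 58% power, against 86% with adjustment (residual SD 10.69).

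**5. Chance imbalance, if the raw score is tested and the baseline SD is also 11.6 (both assumptions).** The standard error of the baseline difference is 11.6 × √(2/44) = 2.47 points. An imbalance of one standard error moves the expected unadjusted follow-up difference by r × 2.47:

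- r = 0.5: 1.24 points, or 18% of the 7-point target.
- r = 0.7: 1.73 points, or 25% of the target.

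**6. Timing.** Entry is 0 to 3 months after onset and T4 is 12 months after enrolment. T4 therefore falls between 12 and 12 + 3 = 15 months after onset, beyond the one year given in the Discussion.

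**The case against.** The strongest reply is that efficiency is not an error. After 1:1 randomisation the unadjusted tests keep their type I error and are unbiased on average, and ordinary chance imbalance is already reflected in the standard error. The sample size was computed for this comparison and reproduces. The trial loses nothing against its own plan; it passes over a gain. This stands and limits the strength of the point.

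It is also fair that the list of tests is open and that an article condenses the full protocol. But the article does name the tests for the between-arm comparison. With two arms at one visit, ANOVA without a covariate is the t-test, and no adjustment is hinted at. The point rests on a stated choice.

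A reader might infer more than the documents support:

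- **That the result will be biased.** It will not be, on average. The issue is precision and the estimate from this one trial.
- **That raw scores are compared, so that baseline never enters.** The article does not say whether the score or the change is tested. If it is change, baseline does enter, and the gain is that of Reading B.
- **That a power gain to 97% is established.** It depends on an assumed correlation and on Reading A.
- **That patients who miss a visit will be dropped.** The article states no missing-data rule. That detail is commonly left to the analysis plan, so its absence is no finding.
- **That time since onset is a recorded study variable.** Table 1 does not list it. It must be known to check eligibility, but its gain beyond baseline FMA cannot be computed from the article.

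**Conclusion.** The point holds as a recommended improvement, not as a flaw that invalidates the analysis. The stated comparison is unadjusted, made visit by visit, and leaves the choice between mean and rank comparison to the data.

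At 44 per arm, baseline adjustment raises power from 79.9% to between about 83% and 97% under Reading A (r from 0.3 to 0.7), or to between about 86% and 90% under Reading B (r from 0.7 down to 0.5). The direction is the same under each reading examined. The size rests on the assumed r, on two-sided testing, on equal SDs at both visits for the change-score calculations, and on what 11.6 represents, which the article leaves open.

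The Discussion's follow-up time does conflict with Table 1 and the entry criterion. This is a separate, minor matter of wording and is no evidence about the choice of test.

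**What to change.** Pre-specify one primary model for FMA in all randomised patients, analysed as allocated. Either of two forms will do:

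- ANCOVA at one named visit, adjusted for T0 FMA.
- A mixed model over T1 to T4, adjusted for T0 FMA, with the arm contrast read at that visit.

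The sponsor has to choose the visit, since the article names none; T4 is one option. Time from stroke onset to T0 may be added as a covariate if the onset date is recorded. Keep Mann-Whitney as a sensitivity analysis only.

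In the Sample Size section, state whether 11.6 is the SD of the follow-up score or of change, so that the calculation and the analysis refer to the same quantity. Separately, reconcile the Discussion's follow-up time with the enrolment-based visit schedule.

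The cost is wording only. No extra patients, visits or FMA measurements are needed.

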### Outcomes

The primary endpoint of WP1 is comparison of sensorimotor disability after self-rehabilitation vs. usual care treatment. Accordingly, its primary outcome is Fugl-Meyer assessment (FMA), which comprises five domains (155 items in total) as follows: motor function of the upper and lower extremities; sensation, tested through a light touch on two surfaces of the arm and leg, as well as position sense for eight joints; balance, three seated and four standing tests; joint range of motion, testing eight joints; and joint pain. Items are scored on the basis of ability to complete the item, according to which 0 = cannot perform; 1 = performs partially; and 2 = performs fully. The maximum total scale score is 226. Points are divided among the domains as follows: the motor function score ranges from 0 (hemiplegia) to 100 points (normal motor performance) and is divided into 66 points for the upper extremities and 34 points for the lower extremities; the sensation score ranges from 0 to 24 points and is divided into 8 points for light touch and 16 points for position sense; the balance score ranges from 0 to 14 points and is divided into 6 points for sitting and 8 points for standing; the joint range of motion and pain scores range from 0 to 44 points (13).

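### Arms are compared only by unadjusted tests at each visit, and the within-arm tests added at p < 0.05 cannot separate treatment from recovery common to both arms; WP1 should rest on one baseline-adjusted between-arm analysis.

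*Protocol article*

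**What the plan says.** Under Outcomes, the main question is a contrast between arms: "The primary endpoint of WP1 is comparison of sensorimotor disability after self-rehabilitation vs. usual care treatment". Under Data Analysis, three kinds of analysis are described beyond descriptive statistics.

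- **Between arms.** For WP1 the arms are compared "with regard to the outcomes considered at each time point of the various evaluation times", by t-test or ANOVA, or by Kruskal-Wallis or Mann-Whitney. For WP2 to WP7, "comparisons between groups at different times will be assessed using parametric tests" or their non-parametric counterparts. No baseline covariate, change score or arm-by-time term is named.
- **Correlation and regression.** "For each variable considered, both longitudinally and transversely, correlation and regression analyses will also be performed". These are not described as comparing the arms.
- **Within arm, over time.** As a further item, "for each WP we will perform longitudinal intragroup comparisons at different times by means of parametric tests", namely the t-test and ANOVA, or "non-parametric tests, such as the Friedman test and the Wilcoxon test, depending on data distribution".

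The section closes by setting p < 0.05 for all tests, so the within-arm comparisons are hypothesis tests. Descriptive statistics are listed separately at the start of the section.

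Patients enter at "no more than 3 months since stroke onset" (Participants). The Discussion says the trial will "follow up stroke patients from subacute stroke to the chronic phase, up to 1 year after stroke onset". Table 1 schedules the FMA, Oxford Cognitive Screen and Barthel Index at T0 and at 3, 6, 9 and 12 months.

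**The concern.** Randomisation protects the contrast between arms. It does not protect a before/after comparison inside one arm. Patients enrolled in the subacute phase and followed to the chronic phase can be expected to change whichever arm they are in, and both arms receive some form of rehabilitation. A within-arm change therefore mixes the allocated treatment with recovery common to both arms and with repeat testing. A small p-value in the self-rehabilitation arm does not show an effect of self-rehabilitation, and a significant result in one arm only does not show a difference between arms. The plan says nothing to keep these p-values from being read that way.

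The second issue is efficiency. The outcomes are all measured at baseline, yet the arm comparison as described does not use that measurement. In a single-centre trial that names enrolment among its own likely problems, this gives up precision that is already paid for.

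**Working it through.** **Inputs.** From Sample Size: 44 per arm, a difference of 7 FMA points, SD 11.6, 80% power, α 5%. Sidedness is not stated. The article does not say whether 11.6 is an SD of scores or of change, and it gives no expected size of common recovery. The gains, the change SDs and the baseline correlations below are therefore assumptions, shown over a range.

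**1. The plan's own figure.** Two-sided, normal approximation:

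n per arm = 2 × (1.960 + 0.842)² × 11.6² / 7² = 2 × 7.849 × 134.56 / 49 = 43.1, rounded up to 44.

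Power at 44 per arm is 0.808 (normal) or 0.799 (t distribution). A one-sided test would need 34, so the calculation is two-sided. The stated 44 per group reproduces.

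**2. Within-arm test with no treatment effect.** Both arms have the same true mean gain m. The paired t-test in one arm (n = 44, 43 degrees of freedom) has noncentrality m / (SD of change / √44). With a change SD of 11.6, the standard error is 11.6 / 6.633 = 1.749. With p the within-arm rejection probability and independent arms, the chance that exactly one arm is significant is 2p(1 − p).

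| Common gain | Noncentrality | Within-arm p < 0.05 | One arm significant, the other not |
|---|---|---|---|
| 3 | 1.72 | 38.9% | 2 × 0.389 × 0.611 = 47.5% |
| 5 | 2.86 | 79.8% | 2 × 0.798 × 0.202 = 32.2% |
| 7 | 4.00 | 97.5% | about 5% |

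A simulation of 20,000 trials per scenario agreed. On the same data, a between-arm t-test of change rejected in 4.8% to 5.0% of trials.

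**3. Sensitivity to the change SD.** If 11.6 is the SD of scores and ρ is the correlation between baseline and follow-up, the change SD is 11.6 × √(2(1 − ρ)).

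| ρ (assumed) | Change SD | Within-arm p < 0.05 at gain 3 / 5 / 7 | Discordant at gain 3 / 5 / 7 |
|---|---|---|---|
| 0.3 | 13.7 | 29% / 66% / 91% | 42% / 45% / 16% |
| 0.5 | 11.6 | 39% / 80% / 97.5% | 48% / 32% / 5% |
| 0.7 | 9.0 | 58% / 95% / 99.9% | 49% / 9% / 0.2% |

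The two problems do not peak together. Chance discordance is most frequent when the within-arm power is near one half. Significance in both arms becomes near certain as the common gain grows.

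**4. Precision given up by the unadjusted comparison.** If 11.6 is the SD of scores, ANCOVA has residual SD 11.6 × √(1 − ρ²). The required n per arm for 7 points is then 43.1 × (1 − ρ²).

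| ρ (assumed) | Follow-up score, unadjusted | Change score | ANCOVA |
|---|---|---|---|
| 0.3 | 44 | 61 | 43.1 × 0.91, so 40 |
| 0.5 | 44 | 44 | 43.1 × 0.75, so 33 |
| 0.7 | 44 | 26 | 43.1 × 0.51, so 22 |

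A simple change score is not a safe replacement, since at ρ = 0.3 it needs more patients than the unadjusted follow-up score. ANCOVA needs fewer than the unadjusted score at each correlation shown.

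**The case against.** The strongest reply is that the primary comparison is already between arms and already valid. Allocation is randomised 1:1, so a difference in 12-month scores estimates the treatment effect and recovery common to both arms cancels out of it. The within-arm tests come last, as an addition, and nothing in the text says efficacy will be judged from them. This stands. A reader might infer that the trial will claim treatment effects from before/after tests, or that a between-arm test of change is required for validity. The documents support neither.

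A reader might also infer that within-arm tests are the only longitudinal analysis and that they are bound to be significant. Longitudinal correlation and regression are planned too, although not as arm comparisons. No size of recovery is given, and at a 3-point gain with a change SD of 11.6 the within-arm test rejects in only about 39% of trials.

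Third, a blanket replacement across all work packages would not fit. For some, such as WP5 on microbiota and WP6 on microRNA, change with recovery is itself the question. In Table 1, DTI, DEXA and microbiota are marked at one visit only, and EEG and the fatigue inventory at T0 and T2 only, so a T4 contrast cannot apply to them. This also stands and limits the fix.

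Finally, model detail is often left to a full analysis plan. That does not dispose of the point. The article is not silent here: it names the tests for the arm comparison, and it commits every work package to within-arm tests at p < 0.05. The objection is to that stated choice.

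**Conclusion.** The point holds as a weakness in the choice of analysis. It is not an error that invalidates the primary comparison. The arm comparison named for WP1 is valid but does not use a baseline measurement that is collected. The within-arm tests cannot separate treatment from shared recovery and carry no label that keeps them from being read as efficacy evidence.

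The within-arm figures rest on 44 evaluable patients per arm, a change SD of 11.6 and an assumed common gain. The ANCOVA figures rest on 11.6 being the SD of scores and on an assumed baseline correlation. Both readings of 11.6 hold together only at ρ = 0.5. Harm from the within-arm tests arises only if their p-values are used as evidence of a treatment effect. The loss of precision does not depend on how results are interpreted.

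**What to change.** For WP1, name one baseline-adjusted between-arm analysis as the sole basis for the treatment effect. This can be ANCOVA of the T4 score with the T0 score as covariate, or a mixed model for repeated measures with baseline as covariate and an arm-by-time term, reporting the T4 difference with its 95% confidence interval. Report WP1 within-arm changes as means with 95% confidence intervals, labelled descriptive and not used as evidence of efficacy.

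In WP2 to WP7, use the same baseline-adjusted contrast for arm comparisons of measures taken at T0 and later, at the last scheduled visit. By Table 1 that is T2 for EEG and the fatigue inventory, and T4 for biochemistry and microRNA. Within-patient tests may stay where change with recovery is itself the question.

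The cost is a change of wording. No new data, visits or patients are needed. The downside is that WP1 within-arm p-values are no longer reported.
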